|                                                                                                                                                                                                                                                                                                                                                                                                                                                                                                                                                                                                                                                                                                                                                                                                                                                                                                                                                                                                                                                                                                                                                                                                                                                                                                                                                                                                                                                                                                                                                                                                                                                                                                                                                                                                                                                                                                                                                                                                                                                                                                                                                                                                                                                                                                                                                                                                                                                  |
|--------------------------------------------------------------------------------------------------------------------------------------------------------------------------------------------------------------------------------------------------------------------------------------------------------------------------------------------------------------------------------------------------------------------------------------------------------------------------------------------------------------------------------------------------------------------------------------------------------------------------------------------------------------------------------------------------------------------------------------------------------------------------------------------------------------------------------------------------------------------------------------------------------------------------------------------------------------------------------------------------------------------------------------------------------------------------------------------------------------------------------------------------------------------------------------------------------------------------------------------------------------------------------------------------------------------------------------------------------------------------------------------------------------------------------------------------------------------------------------------------------------------------------------------------------------------------------------------------------------------------------------------------------------------------------------------------------------------------------------------------------------------------------------------------------------------------------------------------------------------------------------------------------------------------------------------------------------------------------------------------------------------------------------------------------------------------------------------------------------------------------------------------------------------------------------------------------------------------------------------------------------------------------------------------------------------------------------------------------------------------------------------------------------------------------------------------|
| Ospedale dei Castelli, Rome, Italy                                                                                                                                                                                                                                                                                                                                                                                                                                                                                                                                                                                                                                                                                                                                                                                                                                                                                                                                                                                                                                                                                                                                                                                                                                                                                                                                                                                                                                                                                                                                                                                                                                                                                                                                                                                                                                                                                                                                                                                                                                                                                                                                                                                                                                                                                                                                                                                                               |
| 8. Subject population:

Patients aged 40-80 undergoing colonoscopy                                                                                                                                                                                                                                                                                                                                                                                                                                                                                                                                                                                                                                                                                                                                                                                                                                                                                                                                                                                                                                                                                                                                                                                                                                                                                                                                                                                                                                                                                                                                                                                                                                                                                                                                                                                                                                                                                                                                                                                                                                                                                                                                                                                                                                                                                                                                                                  |
| 9. Inclusion/Exclusion criteria:

Inclusion criteria: 
 
Patients aged 40 years or older undergoing screening colonoscopy for CRC
 
Ability to provide written, informed consent (approved by EC) and understand the responsibilities of trial participation.
 
 Exclusion criteria: 
 
subject at high risk for CRC;
 
subjects with a personal history of CRC, IBD or hereditary polyposis or non-polyposis syndromes;
 
patients with previous resection of the sigmoid rectum;
 
patients on anticoagulant therapy, which precludes resection / removal operations due to histopathological findings;
 
patients who perform an emergency colonoscopy.
 
                                                                                                                                                                                                                                                                                                                                                                                                                                                                                                                                                                                                                                                                                                                                                                                                                                                                                                                                                                                                                                                                                                                                                                                                                                                                                                                                                                                                                                                                                                                                                                                                                                            |
| 10. Study groups: Single-arm                                                                                                                                                                                                                                                                                                                                                                                                                                                                                                                                                                                                                                                                                                                                                                                                                                                                                                                                                                                                                                                                                                                                                                                                                                                                                                                                                                                                                                                                                                                                                                                                                                                                                                                                                                                                                                                                                                                                                                                                                                                                                                                                                                                                                                                                                                                                                                                                              |
| 11. Study procedure:

Each patient will undergo standard white-light colonoscopy with the support of the latest version of CE marked GI Genius available.

Each polyp identified during the colonoscopy procedure will be first prepared for being characterized as follows: 
 
white-light examination (use of virtual chromoendoscopy techniques [e.g. NBI, BLI, LCI] will not be allowed in this first step)
 
no zoom
 
washed properly
 
framed at 6 o'clock
 
framed at the nearest distance while keeping it on focus
 
framed steadily
 
 The endoscopist will move around the target polyp until GI Genius CADx will provide an optical diagnosis.

The endoscopist will be asked to predict polyp's histology at this stage and will categorize it as either adenoma or non-adenoma along with the confidence of his assessment. This first prediction will be recorded in the study CRF.

Furthermore, the GI Genius CADx optical diagnosis will be recorded on the study CRF.

Subsequently, the endoscopist will switch on blue light virtual chromoendoscopy (i.e. NBI or BLI) and will be asked to record in the CRF his endoscopic assessment of the polyp: again, the endoscopist will predict polyp's histology at this stage and will categorize it as either adenoma or non-adenoma along with the confidence of his assessment. This second prediction will be recorded in the study CRF. Additionally, endoscopist will record polyp morphology (according to Paris classification), size and location (Cecum, Ascending colon, Transverse colon, Descending colon, Sigmoid colon and Rectum).

All the procedure will be video recorded from the beginning to the end with a recorder directly attached to the endoscopy video processor (prior to GI Genius), so to record the video without any additional overlay (i.e. without GI Genius CADe overlay).

All polyps will be removed, collected separately each from the other and stored in formaline at 10% to be analyzed by the local pathologists. All lesions will be classified by the pathologist according to the classification of Vienna. An advanced adenoma is defined as adenoma of 10 mm and/or with a villous component > 20% and/or high-grade dysplasia. Histology results will be recorded in the study CRF. |

After the procedure has been carried out and data provided by the endoscopist has been properly recorded, before the availability of the histology results, without the presence of the patient and the endoscopist, the video recording will be reviewed by a team of endoscopists to get their optical biopsies and confidence about polyp adenomatous or non-adenomatous histology.

## **12. Follow-up schedule:**

There will be no patient follow-up

## **13. Timeline:**

First patient: May 2021  
End of Study: August 2021

## **14. Study endpoints:**

### **Primary endpoint:**

- Negative Predictive Value (NPV) of GI Genius CADx optical diagnosis on diminutive ( $\leq 5$  mm) rectosigmoid polyps.

### **Exploratory endpoints:**

1. Agreement in assignment of post-polypectomy surveillance intervals according to PIVI guidelines between:
  - the assignment identified according to the combined GI Genius CADx optical diagnosis for diminutive ( $\leq 5$  mm) polyps and histology for larger polyps ( $> 5$  mm), and
  - the assignment identified according to histology alone regardless of lesion size.
2. Sensitivity, Specificity, Accuracy, PPV and NPV of GI Genius CADx optical diagnosis
3. Sensitivity, Specificity, Accuracy, PPV and NPV of the optical diagnosis of endoscopists assessing lesions in white-light with the help of GI Genius CADx
4. Sensitivity, Specificity, Accuracy, PPV and NPV of the optical diagnosis of endoscopists assessing lesions with virtual chromoendoscopy and without the help of GI Genius CADx

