## 1.2 Software-aided colon polyp detection

GI Genius (also referred to as CB-17-08) CADe System is an Intelligent Endoscopy Module designed to be an adjunct to video colonoscopy with the purpose of supporting the operating physician with artificial intelligence during Colorectal Cancer Screening and Surveillance procedures.

To make GI Genius CADe System working, the module is placed on a shelf of a standard endoscopy tower and connected to both the video processor and the main display, both using the well-established SDI or HD-SDI video standards. The large part of the currently marketed endoscopy solutions is natively compatible with GI Genius CADe System, the few others can be connected using suitable adaptors.

As a result, the endoscopy video stream is flowing through the module with no modification or delay, without changing the way the endoscopy procedure is carried out.

At the same time, in real time, the module augments the video stream by adding small green overlay markers surrounding areas of interest, such that they can be further inspected and assessed independently according to the established standard clinical practice. Overlaid markers are further notified with a convenient sound.

GI Genius CADe System gives full control to the operating physician, being able to enable or disable the overlay markers at any time with a single touch.

**Figure 1.** GI Genius system on video endoscopy trolley.

[figure not shown]

[figure not shown]

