## **2. Colonoscopy visit**

Each eligible patient meeting inclusion/exclusion criteria who have agreed to participate to the study and have signed the ICF will undergo a colonoscopy examination performed by an experienced endoscopist. All polyps (mucosal lesions) detected during the colonoscopy will be removed with standard techniques of polyp resection. Bowel preparation, including split dose, will be done according to the standard protocols of the individual sites. The quality of bowel preparation will be assessed during colonoscopy using the Boston Bowel Preparation Scale (BBPS). Sedation according to the sites best experience and standard procedures will be delivered to the patient. Prior to undergoing colonoscopy, study subjects will undergo placement of intravenous catheter. Sedative medications (Midazolam, Meperidine, Propofol, etc.) will be administered as per local institutional practice if applicable. Women of child bearing potential will undergo a pregnancy test to exclude pregnancy prior to the colonoscopy if foreseen by standard procedures at the investigational site.

Study procedure:

Each patient will undergo standard white-light colonoscopy with the support of the latest version of CE marked GI Genius available.

Each polyp identified during the colonoscopy procedure will be first prepared for being characterized as follows:

white-light examination (use of virtual chromoendoscopy techniques [e.g. NBI, BLI, LCI] will not be allowed in this first step)

no zoom

washed properly

framed at 6 o'clock

framed at the nearest distance while keeping it on focus

framed steadily

The endoscopist will move around the target polyp until GI Genius CADx will provide an optical diagnosis.

The endoscopist will be asked to predict polyp's histology at this stage and will categorize it as either adenoma or non-adenoma along with the confidence of his assessment. This first prediction will be recorded in the study CRF.

Furthermore, the GI Genius CADx optical diagnosis will be recorded on the study CRF.

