Subsequently, the endoscopist will switch on blue light virtual chromoendoscopy (i.e. NBI or BLI) and will be asked to record in the CRF his endoscopic assessment of the polyp: again, the endoscopist will predict polyp's histology at this stage and will categorize it as either adenoma or non-adenoma along with the confidence of his assessment. This second prediction will be recorded in the study CRF. Additionally, endoscopist will record polyp morphology (according to Paris classification), size and location (Cecum, Ascending colon, Transverse colon, Descending colon, Sigmoid colon and Rectum).

All the procedure will be video recorded from the beginning to the end with a recorder directly attached to the endoscopy video processor (prior to GI Genius), so to record the video without any additional overlay (i.e. without GI Genius CADe overlay).

All polyps will be removed, collected separately each from the other and stored in formaline at 10% to be analyzed by the local pathologists. All lesions will be classified by the pathologist according to the classification of Vienna. An advanced adenoma is defined as adenoma of 10 mm and/or with a villous component > 20% and/or high-grade dysplasia. Histology results will be recorded in the study CRF.

After the procedure has been carried out and data provided by the endoscopist has been properly recorded, before the availability of the histology results, without the presence of the patient and the endoscopist, the video recording will be reviewed by a team of endoscopists to get their optical biopsies and confidence about polyp adenomatous or non-adenomatous histology.

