## 8 DATA COLLECTION AND MANAGEMENT

### 8.1 Case report form

A case report form (CRF) will capture information regarding patient demographics, indication for procedure, recognition of endoscopic landmarks (caecum reached, colonoscopy is complete), procedure details and safety events, and all the data required for endpoint evaluation.

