### 10.2 Exploratory endpoints:

1. Agreement in assignment of post-polypectomy surveillance intervals of the enrolled patients according to established guidelines between:
  - the combined use of GI Genius CADx as optical diagnosis for diminutive ( $\leq 5$  mm) polyps and conventional histology as diagnostic tool for polyps  $> 5$  mm,
  - and*
  - histology as diagnostic tool for all the resected polyps (regardless of size or location).

2. Sensitivity, Specificity, Accuracy, PPV and NPV of GI Genius CADx optical diagnosis.
3. Sensitivity, Specificity, Accuracy, PPV and NPV of the optical diagnosis of endoscopists assessing lesions in white-light with the help of GI Genius CADx.
4. Sensitivity, Specificity, Accuracy, PPV and NPV of the optical diagnosis of endoscopists assessing lesions with virtual chromoendoscopy and without the help of GI Genius CADx.

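### CHANGE exploratory endpoint 4 is labelled as made without CADx, but the only chromoendoscopy prediction in the CRF comes after the same endoscopist has sought the CADx output for that polyp

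*Protocol*

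**What the plan says.** The label. Item 4 of the exploratory endpoints in the CHANGE synopsis (section 14) covers the sensitivity, specificity, accuracy, PPV and NPV of the "optical diagnosis of endoscopists assessing lesions with virtual chromoendoscopy and without the help of GI Genius CADx". Section 10.2, item 4, repeats it for "endoscopists assessing lesions with virtual chromoendoscopy and without the help of GI Genius CADx", and item 5 of the analysis plan (synopsis section 15) reports the same quantities descriptively. The item before it in each list is the white-light diagnosis made with CADx help.

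The procedure (synopsis section 11; section 7, Colonoscopy visit). For each polyp:

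1. White light only: "The endoscopist will move around the target polyp until GI Genius CADx will provide an optical diagnosis".
2. The endoscopist makes a binary prediction with a confidence level, and this goes in the CRF.
3. "Furthermore, the GI Genius CADx optical diagnosis will be recorded on the study CRF".
4. "Subsequently, the endoscopist will switch on blue light virtual chromoendoscopy (i.e. NBI or BLI"), and the endoscopist predicts the histology again. "This second prediction will be recorded in the study CRF".

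Section 8.1 says that the CRF will hold "all the data required for endpoint evaluation".

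Separately, the same procedure sections have a team of other endoscopists review the video before histology is available. The recorder sits upstream of GI Genius, so the video carries no overlay.

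**The concern.** The label says that the device did not help; the procedure says that the reader already had the device's output. The second prediction is made by the same person, on the same polyp and in the same session, after the CADx output has been sought and after that person has committed to a CADx-assisted call. No blinding, washout or second reader is stated for this step.

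A reader of the report would take the endpoint 4 figures as the performance of endoscopists using chromoendoscopy on their own. If the figures come from the second prediction, they describe chromoendoscopy added to a CADx-assisted assessment, which is a different quantity. The data from the procedure cannot separate the two, because no reading of these polyps by the operating endoscopist precedes the CADx output.

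**Working it through.** The protocol states no figure for this endpoint, so there is none to reproduce. The check is a comparison of texts, followed by an illustration of direction and size.

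**Step 1: which data feed endpoint 4?** No section names the source. The procedure puts two endoscopist predictions per polyp in the CRF: one in white light after CADx, one in blue light. The list has two endoscopist endpoints: item 3 (white light, with CADx) and item 4 (chromoendoscopy, without CADx). They line up one to one. Section 8.1 points to the CRF for endpoint data, and the second prediction is the only chromoendoscopy call that the CHANGE procedure places there. This mapping is an inference, but the text offers no other.

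**Step 2: is that reading unexposed to CADx?** No. The CADx output is sought at step 1 of the procedure, and its entry in the CRF is listed before the switch to blue light.

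**Step 3: does anything undo the exposure?** Section 1.2 describes the operator as "being able to enable or disable the overlay markers at any time with a single touch". That describes what the detection system can do and is not a required step before the blue-light reading. Hiding the markers would not remove knowledge of a diagnosis already seen.

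**Step 4: is every polyp exposed to a label?** No. Section 1.3 says that the device shows a no-prediction message when it cannot decide. The CHANGE sample size text reports no diagnosis for 1 of 23 pilot polyps (1/23 = 4.3%). Without a label there is none to carry over.

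**Step 5: direction and size, where a label exists (illustration only).** Let p_e be the endoscopist's unaided accuracy, p_c the CADx accuracy and c the share of second readings that simply repeat the CADx label. If the remaining readings have unaided accuracy:

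- accuracy of the second reading = (1 − c) × p_e + c × p_c
- shift = c × (p_c − p_e)

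Inputs: p_c = 85% (pilot) and p_e = 87% (assumed for experts), both from the Standalone CADx synopsis, Sample size. The values 75% and 92% for p_e, and all values of c, are assumptions made here.

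| p_e | c = 0 | c = 10% | c = 25% | c = 50% |
|---|---|---|---|---|
| 75% (assumed) | 75.0% | 76.0% | 77.5% | 80.0% |
| 87% (protocol) | 87.0% | 86.8% | 86.5% | 86.0% |
| 92% (assumed) | 92.0% | 91.3% | 90.3% | 88.5% |

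At c = 50%, for example, 0.5 × 87 + 0.5 × 85 = 86.0 and 0.5 × 75 + 0.5 × 85 = 80.0. The pull is always toward 85%: upward when unaided accuracy is lower than that, downward when it is higher.

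Agreement with CADx moves further than accuracy. With independent errors at c = 0, agreement = (1 − c) × [p_e × p_c + (1 − p_e)(1 − p_c)] + c. For 87% and 85% the bracket is 0.7395 + 0.0195 = 0.759, so agreement rises from 75.9% at c = 0 to 0.5 × 0.759 + 0.5 = 88.0% at c = 50%. A small change in accuracy can therefore hide a large dependence on CADx.

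**The case against.** Several points against the concern have force, and they limit it.

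- **A reader might infer that the endpoint cannot be measured at all, or that any statement about unaided chromoendoscopy from the study would be false.** The documents do not support this. Endpoint 4 names no source, and the planned overlay-free video review could supply readings by endoscopists who never saw the CADx output. What fails is the second prediction as the source, and no section assigns the video review to endpoint 4.
- **A reader might infer that the unaided figure is inflated.** The protocol's own figures point the other way: with 87% and 85%, carry-over lowers it, by at most 2 points (full carry-over gives 85%). Only the pull toward CADx is supported.
- **A reader might infer that every polyp is affected.** The no-prediction output rules that out.
- **A reader might infer that the apparent benefit of CADx is diluted.** Items 4 and 5 of the analysis plan are separate descriptive reports, with no planned contrast between them. The two readings also differ in light mode, so their difference would not isolate the device effect even without carry-over.
- **The label may only mean that CADx is not displayed during the blue-light step.** The procedure does not say so. Even on that reading, the wording invites the figure to be taken as unaided performance.
- **A statistical analysis plan may name the source.** It may, but it cannot undo an exposure that the procedure fixes, and the label and the sequence both stand in this protocol.

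The core conflict survives all of these.

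**Conclusion.** The label does not fit the reading. The only chromoendoscopy prediction that the CHANGE procedure puts in the CRF is made after CADx exposure and after a CADx-assisted call, so it cannot support a statement about unaided chromoendoscopy performance. Where CADx gave a label, the reading may be pulled toward it by an unknown amount in either direction. At an assumed 50% carry-over, accuracy moves from 87% to 86% on the protocol's figures, or from an assumed 75% to 80%.

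The conclusion rests on the fixed sequence and on the inference that endpoint 4 uses the second prediction. The size rests on assumed carry-over and cannot be estimated from the protocol.

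The consequence is limited. The endpoint is exploratory and descriptive, with no test attached. The CHANGE primary NPV concerns the CADx output itself, and the reviewers in the Standalone primary comparison see no AI output. Neither is affected. The correction is still worth making, because it changes what the study may claim about endoscopists working without the device.

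**What to change.** 1. In CHANGE synopsis section 14 (item 4), synopsis section 15 (item 5) and section 10.2 (item 4), relabel the second prediction as *virtual chromoendoscopy after CADx-assisted white-light assessment*.
2. Tabulate how often the call changed between the two recorded predictions, separately for polyps with and without a CADx label. Both predictions and the CADx diagnosis are already to be recorded in the CRF.
3. If a CADx-unexposed estimate is wanted, name the planned overlay-free video review as its source and state its limits. The readers differ, they judge video rather than a live procedure, and the clips hold white-light as well as blue-light frames, so it is not a chromoendoscopy-only reading. If the Standalone review is used, it also has an Uncertain option and covers only the first 504 valid lesions.

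Items 1 and 2 cost a wording change and one table, with no new patients or procedures. Item 3 costs more than a re-tabulation, because it changes the readers and the setting and, in the Standalone review, the response options and possibly the lesion set. Relabelling alone resolves the contradiction, so item 3 is optional.
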